## Abstract

**Background:**

Depressive symptoms are common in people with type 2 diabetes and contribute to adverse health consequences that substantially impact social and vocational function. Despite the existence of effective depression treatments, the majority of people with type 2 diabetes do not access these when needed. Web-based alternatives to more traditional psychotherapies offer a potential solution to reducing the personal and economic burdens of type 2 diabetes.

**Objective:**

This paper outlines the protocol for a randomized controlled trial (RCT) of myCompass, a Web-based public health psychotherapy intervention, in people with type 2 diabetes. Fully automated, interactive, and delivered via the Internet without clinician support, myCompass teaches cognitive behavioral therapy-based skills and supports symptom monitoring to improve daily functioning and reduce mild-to-moderate mental health symptoms.

**Methods:**

A two-arm RCT will be conducted. People with type 2 diabetes and mild-to-moderately severe depressive symptoms will be recruited from the community and general practice settings. Screening and enrollment is via an open-access website. Participants will be randomized to use either myCompass or an active placebo program for 8 weeks, followed by a 4-week tailing-off period. The placebo program is matched to myCompass on mode of delivery, interactivity, and duration. Outcomes will be assessed at baseline and at 3-month, 6-month, and 12-month follow-up. The primary study outcome is work and social functioning. Secondary study outcomes include depressive and anxious symptoms, diabetes-related distress, self-care behaviors, and glycemic control.

**Results:**

Nationwide recruitment is currently underway with the aim of recruiting 600 people with type 2 diabetes. Recruitment will continue until October 2017.

**Conclusions:**

This is the first known trial of a Web-based psychotherapy program that is not diabetes specific for improving social and vocational function in people with type 2 diabetes and mild-to-moderately severe depressive symptoms. With the increasing prevalence of type 2 diabetes and depression, a potentially scalable public health intervention could play a very large role in reducing unmet mental health need and ameliorating the personal and societal impact of illness comorbidity.

**Trial Registration:**

Australian New Zealand Clinical Trials Registry (ANZCTR) Number: ACTRN12615000931572; https://www.anzctr.org.au/Trial/Registration/TrialReview.aspx?id=368109 (Archived by WebCite at http://www.webcitation.org/ 6rh3imVMh)

## Introduction

### Background

Type 2 diabetes is a common chronic and disabling disease and a major contributor to global disease burden [1]. Depression is frequently comorbid with type 2 diabetes and contributes independently to a range of adverse health outcomes that substantially compromise social and vocational functioning. These include greater diabetes symptom burden, poorer self-care, and increased risk of micro- and macrovascular complications and mortality [2]. In addition, the economic impact of disease comorbidity is considerable with functional disability, functional dependence, workplace productivity losses, health service use, and health care costs higher for people with both conditions than those with diabetes alone [2,3].

Research supports a bidirectional relationship between type 2 diabetes and depression [4]. Findings supporting increased risk of type 2 diabetes in people with depression [5] are generally explained with reference to physiological (eg, hypothalamic- pituitary-adrenal axis dysfunction [6]), motivational (eg, poorer self-care, adiposity, and inactivity [6,7]), and/or pharmacologic (eg, impact of antidepressant medication on glycemic control [5]) factors. At the same time, increased risk of depression in people with type 2 diabetes is generally attributed to the emotional burden of living with a complex and demanding disease that often intrudes into normal lifestyle [8]. The likelihood of a reciprocal relationship between type 2 diabetes and depression makes the personal and societal impact of illness comorbidity potentially immeasurable [4].

Despite the existence of evidence-based therapies for depression in diabetes, including cognitive behavioral therapy (CBT) and antidepressant medication, upward of 60% of people with comorbid conditions do not receive mental health treatment [9]. In the primary health care setting, where most people with type 2 diabetes access medical treatment, low screening rates mean that depressive symptoms are often missed [9] and only a minority of patients who screen positive accept a referral for face-to-face support [10]. At the same time, personal, social, and structural barriers to seeking help—including privacy concerns and stigma, lack of support and poor relationships with health care providers, time and lifestyle constraints, financial cost, and lack of service availability—compromise access to satisfactory mental health care for many patients [11,12]. There is considerable opportunity, therefore, to reduce the personal and societal burden of illness by facilitating greater access to more flexible and cost-efficient mental health treatments for this patient group.

Internet delivery of evidence-based psychological therapies is a popular, clinically effective, and cost-effective means of increasing treatment reach; a small number of Web-based diabetes-specific interventions that directly target depression have been evaluated [13]. These include van Bastelaar et al’s [14] adaptation of Lewinsohn’s Coping with Depression Program and Nobis et al’s [15] application of systematic behavioral activation and problem-solving therapy (ie, GesundheitsTraining.Online Mood Enhancer Diabetes [GET.ON MED]). Findings from these studies establish the symptom benefits of Internet-delivered self-help for diabetes patients with clinically relevant levels of depressive symptomatology. However, subthreshold depression is more prevalent in type 2 diabetes than clinical depression and is associated with increased functional limitation and disability, including reduced social and vocational performance [16,17]. As such, the effectiveness of electronically delivered psychotherapy as a treatment approach for type 2 patients with mild-to-moderate depressive symptoms also warrants rigorous scientific attention.

Proudfoot et al [18] have previously published controlled data showing that mild-to-moderate mental health symptoms— including symptoms of depression, anxiety, and stress—are reduced following use of the broadly available Web-based program, myCompass, with treatment benefits extending to work and social functioning. More recently, in an uncontrolled pilot study, myCompass showed promise as an acceptable and effective treatment for depression and functional disability in people with type 1 and type 2 diabetes [19]. myCompass differs from the interventions described in van Bastelaar et al [14] and Nobis et al [15] in that it is a fully automated (ie, no therapist input) public health program that is generic in its therapeutic content (ie, not diabetes sensitive). An intervention approach that is capable of treating depressive symptoms without disease-specific modification is potentially a more efficient and accessible alternative to meeting the unmet mental health needs of people with type 2 diabetes. Generic skills may also assist the increasing number of individuals experiencing multi-morbidity, for whom depression co-occurs with somatic symptoms of multiple illnesses (eg, diabetes, heart disease, hypertension, and kidney disease) [20,21]. From a primary care perspective, a public health program may have important pragmatic advantages in the primary care setting, where time pressures often impede dissemination of, and prohibit practitioner training in, multiple disease-specific tools, and where treatment of multi-morbidity and undifferentiated physical and mental health symptoms is particularly relevant.

### Objectives

This paper was prepared using the Standard Protocol Items: Recommendations for Interventional Trials (SPIRIT) guidance for presenting clinical trial protocols [22] and the Consolidated Standards of Reporting Trials of Electronic and Mobile HEalth Applications and onLine TeleHealth (CONSORT-EHEALTH) checklist [23]. The paper describes a randomized controlled trial (RCT) of the Web-based intervention, myCompass, in patients with comorbid type 2 diabetes and mild-to-moderately severe depressive symptoms. The primary aim of this RCT, called SpringboarD, is to determine whether treatment with myCompass improves work and social function for people with type 2 diabetes and mild-to-moderate depressive symptoms. As functional disability predicts further functional deterioration, functional dependence, and increased use of health services and health care costs [16], depression treatments that improve work and social functioning may substantially reduce the personal and economic burden of comorbid depression and type 2 diabetes. Specifically, we hypothesize that the intervention group will show significant improvement in self-reported functioning socially and in the workplace compared with a placebo-controlled condition.

Our secondary aim is to evaluate the impact of myCompass on a range of symptom- and disease-related variables known to impact a patient’s disease management and blood glucose control. Specifically, in addition to depressive symptoms, we will examine whether myCompass is more effective than a placebo condition in improving anxiety symptoms and diabetes-related distress. Defined as a person’s emotional adjustment to the chronic stressors specific to diabetes, diabetes-related distress is of particular interest due to its greater prevalence and potential role in mediating the relationship between depression and glycemic control [24]. While we have preliminary evidence suggesting that diabetes-related distress may improve following treatment with myCompass [19], replication of this finding in a controlled study is required.

### Trial Design

The study is designed as a two-arm individually randomized RCT and is conducted entirely online. Participants allocated to the intervention group have full access to the myCompass program for 8 weeks, followed by a 4-week tailing-off period to facilitate maintenance. Participants randomized to the control group have access to a placebo Internet-delivered program that is matched to myCompass on mode and duration of delivery and interactivity, but is void of therapeutic content. Participants in both groups have uninterrupted access to treatment as usual for their diabetes during the study.

## Methods

### Participants, Interventions, and Outcomes

#### Study Setting

The setting for this study is Australia. An estimated 1 million Australian adults—5% of the population—had self-reported type 2 diabetes in September 2016, and rates are similar across metropolitan, regional, and remote areas [25].

#### Eligibility Criteria

This study focuses on adults with type 2 diabetes and mild-to-moderately severe depressive symptoms. People are eligible to take part if they are aged 18-75 years, screen positive for depression on the 2-item Patient Health Questionnaire (PHQ-2) (ie, score ≥2) [26], and have access to an Internet-enabled device (eg, computer, tablet, and/or mobile phone). People who screen positive for depression complete the full 9-item Patient Health Questionnaire (PHQ-9) at screening so that the level of symptom severity can be determined.

Exclusion criteria include inability to read English with ease, severe depressive symptoms on the full PHQ-9 (ie, score >19), probable psychosis as measured by the psychosis screener developed for the Australian National Mental Health and Wellbeing Survey [27], currently receiving face-to-face counseling or therapy for depression, changed antidepressant medication in the previous 2 months, high suicide risk as assessed by item 9 of the PHQ-9, and previous use of the myCompass program.

#### Interventions

##### Active Intervention

The active intervention, myCompass [28], is a fully automated, self-help, public health intervention that is tailored to the user and has no therapist involvement in its delivery. Program tailoring occurs via users’ responses to a symptom profiler completed at registration. In-built algorithms target the user’s most salient symptoms and provide recommendations about the symptoms and/or behaviors they might consider monitoring and the treatment modules likely to be of greatest therapeutic benefit. There is flexibility, however, for users to choose their own set of self-monitoring dimensions and treatment modules (see Figures 1-4).

Self-monitoring of symptoms and lifestyle factors occurs in real time via mobile (eg, phone or tablet) and stationary (eg, desktop computer) devices. Users can self-monitor up to three symptoms and behaviors of their choice at any one time—selected from a list of 20—or three that are recommended to them by the program. Each symptom is rated on a 10-point scale. At the time of rating, users also provide contextual information about where they are, what they are doing, and who they are with using a series of drop-down menus. Users can schedule short message service (SMS) text message or email reminders to facilitate self-monitoring—frequency of reminders is determined by the user; receive and print graphical feedback about their monitoring, including contextual information, on their phone or computer to monitor change and assist identification of triggers; and elect to receive helpful facts, mental health care tips, or motivational statements by SMS text message or email.

myCompass treatment modules were developed by mental health professionals at the Black Dog Institute in Sydney, Australia. The program contains 14 skill-building modules derived from CBT, interpersonal psychotherapy, problem-solving therapy, and positive psychology that are interactive and available for completion on computer and tablet devices. Module content covers topics such as *Managing Fear and Anxiety*, *Tackling Unhelpful Thinking*, *Managing Loss and Major Life Change*, and *Solving Problems*. Each module comprises three 10-minute sessions and includes home practice tasks for completion between the weekly sessions to promote skill generalization. The module targeting stress in diabetes has been deactivated for trial participants, to ensure that the intervention is a generic public health program. Participants are encouraged to complete at least three modules during the intervention period, during their own time.

User privacy is managed by a password-protected log-on and by ensuring that user-generated data (ie, self-monitoring ratings) are not stored on the user’s phone, but are instead transferred via the Internet using Secure Sockets Layer protocol, which encrypts transmitted data by rendering it unreadable to anyone other than the intended recipient, and by storing the data in secure servers. The data is reidentifiable only with the list of study participant codes, to which only the named researchers will have access and which will be stored in a password-protected file separate from the study data. Registering to use myCompass is free and users are not billed for the SMS text messages they receive.

Participants randomized to myCompass have access to the full program for 8 weeks, followed by a 4-week tailing-off period during which only the symptom-monitoring function will be accessible. Research has shown that adherence with online interventions is improved when users receive program feedback that is personalized in its content [29]. For this reason, myCompass users receive automated personalized feedback via email about their use of the program’s self-monitoring and module functions at fixed intervals (ie, weeks 1, 3, 5, and 7).

**Figure 1 figure1:**
[figure not shown]
Screenshot of myCompass landing page.

**Figure 2 figure2:**
[figure not shown]
Screenshot of myCompass self-monitoring page.

**Figure 3 figure3:**
[figure not shown]
Screenshot of a page from the myCompass module Tackling Unhelpful Thinking.

**Figure 4 figure4:**
[figure not shown]
Screenshot of myCompass graphical feedback.

##### Placebo Intervention

The placebo program, Healthy Lifestyles, was adapted from a control program used in previous studies by members of the research team. Like myCompass, the program offers users program tailoring at the outset, followed by access to a range of interactive modules containing health- and lifestyle-related information, including skin care and eye health. It contains no therapeutic content, has high face validity as a health and lifestyle intervention, and has previously shown no symptom impact [30]. Participants have full access to the placebo condition for 8 weeks, plus a 4-week tailing-off period (see Figures 5-7).

To further replicate the interactivity of myCompass, users of the placebo program receive an email at weeks 1, 3, 5, and 7 containing a brief reminder to log into the program, but no feedback about their use of the program. They also receive a weekly email containing a factual statement about a health or lifestyle issue.

**Figure 5 figure5:**
[figure not shown]
Screenshot of landing page for placebo program, Healthy Lifestyles.

**Figure 6 figure6:**
[figure not shown]
Page from the Healthy Lifestyles module, The Skin You Live In.

**Figure 7 figure7:**
[figure not shown]
Sample interactive task from the Healthy Lifestyles module.

**Table 1 table1:** Assessments completed at assessment phases.

Assessments		Assessment phase			
		T1^a^	T2^b^	T3^c^	T4^d^
**Baseline**						
	Demographic data	X			
	Disease/treatment data	X	X	X	X
	Mental health history	X			
Primary outcome	Work and Social Adjustment Scale [31]	X	X	X	X
**Secondary outcomes**						
	Patient Health Questionnaire-9 [26]	X	X	X	X
	Diabetes Distress Scale [32]	X	X	X	X
	Generalized Anxiety Disorder Scale [33]	X	X	X	X
	Self-Management Profile for Type 2 Diabetes Scale (behavior items only) [34]	X	X	X	X
	Glycosylated hemoglobin (HbA1c)	X		X	X
	Days out of role [35]	X	X	X	X
	Health service utilization	X	X	X	X

^a^T1: baseline assessment and allocation to intervention or placebo group.

^b^T2: completion of intervention period and online postintervention assessment.

^c^T3: completion of 6-month follow-up assessment.

^d^T4: completion of 12-month follow-up assessment.

#### Outcomes

A summary of assessments completed online by participants at baseline, postintervention, and follow-up is presented in Table 1 [26,31-35].

The primary outcome is work and social functioning, which is measured by the Work and Social Adjustment Scale (WSAS) [31]. The WSAS is a psychometrically sound measure of the impact of mental health problems on daily functioning in five domains: work, social leisure activities, private leisure activities, home management, and personal relationships [31,36]. Scores range from 0 to 40, with higher scores indicating poorer adjustment.

Secondary outcomes include the PHQ-9, the Diabetes Distress Scale [32], the 7-item Generalized Anxiety Scale [33], and the Self-Management Profile for Type 2 Diabetes Scale [34].

At baseline and again at 6- and 12-month follow-up, glycosylated hemoglobin (HbA1c) data will also be collected from participants’ medical records, with their consent. The HbA1c test is a blood test showing a person's average blood glucose level over the previous 3 months and is measured as part of routine clinical care to monitor long-term blood sugar control in people with diabetes. In all cases, the most recent result will be obtained.

Additional measurements include collection of disease-related data (eg, age of onset and treatment regimen), sociodemographic data (eg, age, gender, education, and occupation), and mental health history data (eg, service use and previous diagnoses) at baseline. Service utilization and supports, including medication, received for problems related to mental health and diabetes are also assessed at each assessment point. Days out of role are measured using an item from the World Health Organization Disability Assessment Schedule that asks people to note the number of days in the previous 30 that they were completely unable to perform their work or normal activities because of problems with their physical or mental health [35].

At the conclusion of the trial, data indicating the extent of participant engagement with myCompass will be extracted from the program, including frequency of log-ins, number of modules started and completed, and self-monitoring frequency.

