#### Participant Timeline

Participant consent, screening, and assessment takes place online via a secure study-specific website [37]. After providing informed consent, potential participants complete the online screening tool to determine eligibility. Unsuitable candidates receive automated feedback explaining the reason for their ineligibility; details of crisis supports and other self-help and face-to-face resources are provided to individuals, as appropriate.

Eligible candidates are registered in a secure Web-based platform where they complete the baseline questionnaire and are immediately allocated randomly to either the intervention program or control program for a period of 12 weeks. Subsequent assessment points coincide for both groups at postintervention (12 weeks) as well as 6 and 12 months after randomization (see Figure 8).

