### Data Collection, Management, and Analysis

#### Data Collection

The majority of primary and secondary outcome data is being collected electronically via standardized self-report questionnaires that are completed by logging into the SpringboarD study website (described above). At each assessment point, the website sends a unique link to the study questionnaire via email. Questionnaire data is maintained on a secure server at the University of New South Wales (UNSW) Sydney and is downloaded periodically for storage in a password-protected data file accessible by two project personnel (JC and SS). HbA1c data is collected from each participant’s general practitioner (GP) via phone, mail, and/or facsimile.

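### The HbA1c selection rule sets no date limit, so a 6-month value can predate randomization and dilute the 6-month contrast, and one draw can serve two visits

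*Protocol article*

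**What the plan says.** Table 1 of the protocol article lists HbA1c as a secondary outcome at baseline, 6 months and 12 months. No blood draw for the trial is described. Under Outcomes, "glycosylated hemoglobin (HbA1c) data will also be collected from participants’ medical records, with their consent", and the test "is measured as part of routine clinical care to monitor long-term blood sugar control in people with diabetes". The same paragraph ends with the selection rule: "In all cases, the most recent result will be obtained". It also gives the look-back of the measure: "The HbA1c test is a blood test showing a person's average blood glucose level over the previous 3 months".

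Data Collection adds only the route: "HbA1c data is collected from each participant’s general practitioner (GP) via phone, mail, and/or facsimile". Participant Timeline places the assessments at "postintervention (12 weeks) as well as 6 and 12 months after randomization" and gives the program period as 12 weeks. Statistical Analysis applies MMRM to primary and secondary outcomes, with between-arm contrasts at the nominal time points.

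Nowhere does the article give an earliest acceptable date for a follow-up HbA1c or a window around 6 or 12 months. Nor does it say that a result already used at one visit may not be used at the next.

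**The concern.** Routine care, not the trial schedule, decides when blood is drawn. Taking the latest result on file at a visit therefore gives a value of unknown age. Three things can follow:

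- A participant not tested since randomization contributes the baseline result again as the 6-month outcome.
- A participant last tested during the program contributes a value that, given the 3-month look-back, partly averages glucose from before randomization.
- A participant not tested between months 6 and 12 contributes one blood sample to both follow-up visits.

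The rule acts like carrying the last observation forward, but at data collection. An absent visit value is replaced by an older one before the model sees it, so the MMRM treats it as observed.

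At stake is the reading of the 6-month glycemic contrast. A small or null difference could reflect no effect or old samples, and without draw dates the two cannot be told apart.

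**Working it through.** **The plan's own figure.** No effect size, SD, power or testing interval is given for HbA1c. The only stated calculation is for WSAS: d=0.3, alpha .05, power 80%, 175 per arm. It reproduces as 2 × (1.960 + 0.842)² / 0.3² = 174.4, rounded up to 175. It does not bear on this point.

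**Inputs from the article.** Visits at 6 and 12 months after randomization; a 12-week program (84 / 30.44 = 2.76 months); a 3-month look-back.

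**Assumptions, not in the article.**
- Routine tests are regular, every L months, with random phase. The age of the latest result at a visit is then uniform on (0, L).
- For the share of effect captured, the effect on HbA1c builds linearly over the first 3 months after randomization and then holds.

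**Formulas for a visit at month t.**
- Drawn before randomization: max(0, 1 − t/L).
- Drawn before week 12: max(0, 1 − (t − 2.76)/L).
- Share of effect captured: mean over age of (t − age)/3, limited to the range 0 to 1.
- 12-month value is the same draw as the 6-month value: max(0, 1 − 6/L).

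| L (months) | 6-mo: before randomization | 6-mo: before week 12 | 6-mo: effect captured | 12-mo: before randomization | 12-mo: effect captured | 12-mo: same draw as 6-mo |
|---|---|---|---|---|---|---|
| 3 | 0% | 0% | 100% | 0% | 100% | 0% |
| 4 | 0% | 19% | 96% | 0% | 100% | 0% |
| 6 | 0% | 46% | 75% | 0% | 100% | 0% |
| 9 | 33% | 64% | 50% | 0% | 100% | 33% |
| 12 | 50% | 73% | 37.5% | 0% | 87.5% | 50% |

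For L=12 at 6 months, ages 0 to 3 capture the full effect, ages 3 to 6 capture half on average, and older values capture none: (3 + 1.5)/12 = 37.5%. At 12 months, ages 0 to 9 capture all of it and ages 9 to 12 half: (9 + 1.5)/12 = 87.5%.

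**Sensitivity to the testing pattern.** With irregular (exponential) gaps averaging 6 months, the share predating randomization is exp(−6/6) = 37% at 6 months and exp(−12/6) = 14% at 12 months. With regular tests every 18 months, it is 67% and 33%.

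**Illustration of cost.** Suppose d=0.3 for HbA1c as well (borrowed from WSAS; the article gives none) and 300 × 0.6 = 180 per arm. If a share f of values carries no effect, the observed d is 0.3(1 − f). Power in a plain two-group comparison is 81% at f=0, 51% at f=30% and 30% at f=50%. If the f=50% of stale values are dropped instead, 90 per arm remain with d=0.3: 0.3 × √(90/2) = 2.01, and Φ(2.01 − 1.96) is about 52%. In this setting, dropping stale values costs less power than keeping them.

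**The case against.** The strongest reply is that the size rests on a testing interval the article does not give. With tests every 3 or 4 months, the 6-month contrast keeps 100% or 96% of the effect. This stands: the supportable range at 6 months is from negligible to large.

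A reader might infer that both follow-up contrasts are biased and that a null HbA1c result could not be interpreted at all. The documents do not support that. For regular testing at intervals up to 12 months, no 12-month value predates randomization, and the 12-month contrast keeps at least 87.5% of the effect. Only longer or irregular gaps reach it. Dilution also needs a true effect and test timing that does not differ by arm. If the program changed GP attendance, the error could be differential and its direction unknown.

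A reader might also infer that repeated values distort the MMRM covariance and standard errors. That has not been shown. Duplicates raise the between-visit correlation, which a flexible covariance can estimate, and the article fixes no structure.

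Tight visit windows would be expensive. Under the same model, a window of 4.5 to 8 months contains a draw for 3.5/L of participants: 58%, 39% and 29% for L of 6, 9 and 12. So 42%, 61% and 71% of 6-month values would be missing before attrition. This is a good reason not to prescribe such windows.

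Finally, draw dates and windows are often left to a full protocol or SAP, and the article does not say that dates go unrecorded. That is fair for the missing detail. It does not rescue the rule, which is stated for all cases and, followed as written, admits pre-randomization and duplicated results.

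**Conclusion.** The concern holds in limited form. The article states an undated selection rule for routine-care HbA1c, and nothing else in it restricts that rule. Stale or repeated draws can therefore enter as follow-up outcomes.

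The consequence falls mainly on the 6-month contrast. If there is a true effect and test timing is unrelated to arm, that contrast shrinks toward zero, by nothing at a 3-month testing interval and by well over half at a 12-month interval. The 12-month contrast is little affected for regular testing up to every 12 months, although up to half of its values may then repeat the 6-month draw. The figures rest on assumed regular testing and, for the share captured, on an assumed 3-month linear build-up.

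This concerns one secondary outcome. The primary WSAS analysis, the sample size and the self-report outcomes are not affected.

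**What to change.** Replace the undated rule with the following:

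1. Record the draw date with every HbA1c value, adding it to the GP request if it is not already there.
2. Accept a follow-up value only if it was drawn after randomization, and preferably after the 12-week program.
3. Never use one draw for two visits.
4. Where no draw qualifies, treat that visit's HbA1c as missing in the MMRM.
5. Keep the current most-recent-result version as a sensitivity analysis.

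Any tighter window around 6 or 12 months is for the sponsor to choose, weighing timing against the data it would lose.

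**Cost.** One data field, a few sentences in the protocol or SAP, and more values counted as missing. Under the regular-testing model, requiring a draw after randomization removes 0%, 33% or 50% of 6-month values for L of 6, 9 or 12. Requiring a draw after week 12 removes 46%, 64% or 73%. Barring reuse removes 0%, 33% or 50% at 12 months. If test frequency is related to glycemic control, this missingness may be informative, so the number of missing values and the draw timing should be reported by arm.
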